### Data analysis and integration

2.6.

Data will be expressed as mean ± standard deviation (SD). Data will be checked for normality using Shapiro–Wilks normality test and log-transformation will be applied when required. For multi-group comparisons depending on PA levels, body composition, or other health-related parameters available, Levene's test will be performed to assess whether the variance is equal between groups; if the variance is heterogeneous, data will be log-transformed before analysis. Regression models will be applied to analyse the complex data. Comparisons between two groups will be assessed by the appropriate test (*T*-test or the non-parametric Mann—Whitney *U*-test). When appropriate, two-way ANOVA will be used to further determine the effects of different factors, in the case of independent categorical variables. ANCOVA analyses including variables such as BMI, age and gender as covariates will be also used, when appropriate. The threshold of significance will be defined at *P* < 0.05. Correlation analyses are also envisaged to study the possible relationships between the candidate biomarkers and PA levels and other health-related parameters. SPSS and R software will be used for general statistical analyses.

Omics data from transcriptomics and miRNomics (subset of the core cohort) will be subjected to an exploratory analysis of data through principal component analysis (PCA) and partial least squares discriminant analysis (PLS-DA) (when appropriate). Analysis of differential gene expression will be performed through *T*-tests, such as Student's or limma, ANOVA, and false discovery rate (FDR) correction. Gene set enrichment analysis and functional and pathway analyses will be performed. Metabolomics datasets will also be processed using PCA and PLS-DA, and metabolite network mapping using KEGG reactant pairs along with Tanimoto similarity.

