#### Participants

2.3.1.

A total of 180 volunteers (core cohort) will be recruited and distributed into two age groups: prepubertal individuals (*n* = 90), including children, from 8 to 10 years, and postpubertal adolescents (*n* = 90) from 13 to 15 years. Each group will include three subgroups (*n* = 30) of subjects with normal weight (NW), overweight (OW), and obesity (OB) as defined by WHO criteria (38). Volunteers will be equally distributed between both sexes in each group and subgroup. The sample size of the core cohort is based on our previous expertise in different projects aimed at identifying biomarkers (mainly gene expression biomarkers analysed in blood cells by omics techniques), in which we used even a lower number of volunteers [e.g., studies (24, 39)]. Moreover, the combination/integration of different types of biomarkers that will be performed (based not only on gene expression, but also considering lipidomic, metabolic and miRNA profiles) makes its more likely to be able to detect significant metabolic differences and more robust biomarkers. Additionally, the number of volunteers of the core cohort is also expected to be sufficient to achieve the required sample size for the intervention study, which was calculated as explained in Section 2.4.

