##### Anthropometric parameters

2.3.2.1.

Weight, height, and waist circumference will be measured by trained nurses to derive BMI, the corresponding standard deviation (SD) and BMI Z score, and waist-to-height values as useful indicators of abdominal obesity and cardiometabolic risk in children. Subjects with a BMI Z score below 1 will be classified as presenting normal-weight; those ranging from 1 to 2 will be defined as subjects with overweight, while obesity is defined by a BMI + 2 SD value (38). Waist circumference will be measured at the midpoint between the iliac crest and the costal margin at the midaxillary line in the standing position at the end of a gentle expiration, and waist percentiles will be calculated according to growth curves (42).

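### The automatic rule of log-transforming whenever Levene's test is significant, for multi-group comparisons, does not cure unequal variances in general and can raise the false-positive rate above that of untransformed ANOVA

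*Protocol article*

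**What the plan says.** Section 2.6 (Data analysis and integration) contains two transformation clauses.

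- **Variance.** The clause opens "For multi-group comparisons depending on PA levels, body composition, or other health-related parameters available, Levene's test will be performed" and ends "if the variance is heterogeneous, data will be log-transformed before analysis". It is worded as an instruction, exempts no variable, and says nothing about what follows if the variances remain unequal.
- **Normality.** After a Shapiro-Wilk check, "log-transformation will be applied when required". This clause leaves room for judgement.

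Two-group comparisons have a sentence of their own ("Comparisons between two groups will be assessed by the appropriate test"), which offers a t-test or Mann-Whitney. No non-parametric or unequal-variance alternative is named for three or more groups. The significance threshold is P < 0.05.

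The groups come from section 2.3.1 (two age groups, each with three weight classes of 30, hence 60 per weight class) and from section 2.6.1, where three physical-activity clusters are derived from the data and so have no fixed size.

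**The concern.** A log stabilises variance when the SD is roughly proportional to the mean. Levene's test does not look for that pattern. It reacts to any difference in spread, including groups with the same mean and different SDs. In that case the log makes things worse in two ways: it changes the hypothesis from arithmetic to geometric means, which then differ although the arithmetic means do not, and it leaves a pooled-variance ANOVA running on unequal variances.

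The scale of analysis, and so the meaning of a result, would also switch from marker to marker according to a pre-test. A cohort built from weight strata makes unequal spread plausible, and data-derived clusters make unequal group sizes plausible. Finally, the wording cannot be carried out on a variable that takes zero or negative values.

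**Working it through.** **Inputs.** From the article: the Levene-then-log rule, threshold 0.05, 180 participants, 60 per weight class, 30 per age-by-weight subgroup. Assumed, because the article gives no SDs: a common mean of 10 and the SDs below. The 0.05 threshold is chosen, not derived, so there is no figure to reproduce.

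**Step 1: what the log does when means are equal.** For a lognormal variable with mean m and CV = SD/m, the geometric mean is m/√(1+CV²) and the log-scale SD is √ln(1+CV²). With m = 10:

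| SD | Geometric mean | Log-scale SD |
|---|---|---|
| 2 | 10/√1.04 = 9.81 | √ln 1.04 = 0.198 |
| 4 | 10/√1.16 = 9.28 | √ln 1.16 = 0.385 |
| 6 | 10/√1.36 = 8.57 | √ln 1.36 = 0.555 |

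Equal means have become unequal geometric means, and the SD ratio is still 0.555/0.198 = 2.8 (it was 3). For normal data the log-scale SD is approximately SD/m, so SDs of 1/2/3 become about 0.1/0.2/0.3 and the ratio is unchanged.

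**Step 2: false-positive rate for equal arithmetic means.** Three groups, 3,000 runs per row. Rule: Levene at 0.05; if significant, one-way ANOVA on logs, otherwise on raw data. Runs containing a value at or below zero were dropped because the log does not exist (at most 104 of 3,000, in a row with normal SDs 1/2/3). The Monte Carlo standard error √(p(1−p)/3000) is about 0.004 at p = 0.05 and 0.009 at p = 0.4.

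| Group sizes | Data, SDs | Raw ANOVA | Rule | Welch ANOVA |
|---|---|---|---|---|
| 60/60/60 | normal 1/1.5/2 | 0.063 | 0.076 | 0.052 |
| 60/60/60 | normal 1/2/3 | 0.053 | 0.141 | 0.042 |
| 60/60/60 | lognormal 2/4/6 | 0.065 | 0.325 | 0.063 |
| 30/30/30 | normal 1/1.5/2 | 0.055 | 0.059 | 0.049 |
| 30/30/30 | normal 1/2/3 | 0.060 | 0.090 | 0.054 |
| 30/30/30 | lognormal 2/4/6 | 0.060 | 0.172 | 0.062 |
| 90/60/30 | normal 1/1.5/2 | 0.122 | 0.139 | 0.056 |
| 90/60/30 | normal 1/2/3 | 0.148 | 0.249 | 0.046 |
| 90/60/30 | lognormal 2/4/6 | 0.158 | 0.416 | 0.069 |
| 30/60/90 | normal 1/1.5/2 | 0.029 | 0.033 | 0.057 |
| 30/60/90 | normal 1/2/3 | 0.019 | 0.057 | 0.048 |
| 30/60/90 | lognormal 2/4/6 | 0.023 | 0.181 | 0.056 |

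Levene triggered the log in 84% to 100% of runs. Among triggered runs, the variances still differed on the log scale in 97% to 100%.

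**Step 3: how much of the excess belongs to the log.** At 90/60/30 with normal SDs 1/2/3, the excess over nominal is 0.249 − 0.05 = 0.199, of which raw ANOVA already carries 0.148 − 0.05 = 0.098. With SDs 1/1.5/2 it carries 0.072 of 0.089. So half or more of the excess in these two rows comes from pooling variances with unequal group sizes, not from the log.

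**Step 4: where the log works.** With equal means and equal variances (lognormal, CV 0.6) the rule's error was 0.038. With a common log-scale SD of 0.6 and medians 1/1.3/1.7, only about 5% of Levene-triggered runs still showed unequal variances after the log.

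**Step 5: variables that are not positive.** Section 2.3.2.1 states: "Subjects with a BMI Z score below 1 will be classified as presenting normal-weight". No lower bound is given, so zero and negative z-scores are eligible. If z in this group were standard normal cut off at 1, the negative share would be Φ(0)/Φ(1) = 0.594. With mean 0.5 and SD 0.4 it would be 0.118, and the chance that all 30 in a subgroup are positive would be (1 − 0.118)³⁰ = 0.023. These distributions are assumptions.

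**The case against.** The strongest reply is that the planned markers are mostly concentrations and expression levels (section 2.5), for which a log is often right and the geometric mean is a legitimate target. This stands, and Step 4 supports it. The fault lies in the automatic trigger, not in the log, and a reader who infers that log-transformation as such is wrong here would go too far.

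It is also fair that equal means with a two- to three-fold SD ratio is an unfavourable case for a log, that no SDs are given, and that the rule can be conservative when the largest group is the most variable (0.033 in one row). The inflation is therefore conditional.

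Four further inferences are tempting and not supported:

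- **BMI z-score will be log-transformed.** The article never names it for this step. It defines the weight strata, and its inferential use is the pre-post analysis of section 2.4, which is not a multi-group comparison and so lies outside the Levene clause. The normality clause could reach it but leaves discretion. What remains is a gap left by unrestricted wording.
- **Two-group comparisons are inflated in the same way.** They have their own sentence, and the Levene clause does not govern them.
- **Normality will be tested on pooled raw data instead of residuals.** The article does not say so, and this detail is commonly left to the full plan.
- **The biomarker selection is compromised.** Section 2.6.1 relies on PLS-DA, sparse PLS, random forest and held-out prediction, and differential expression uses limma or ANOVA with FDR correction. The Levene rule concerns supporting comparisons.

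That an article condenses a fuller plan does not dispose of the point: the sentence states a rule, and the rule as stated would have to change.

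**Conclusion.** The concern holds for the Levene sentence in section 2.6. As a general remedy for unequal variances the rule is unsound: in all 12 rows of the table its error for equal arithmetic means exceeded that of untransformed ANOVA, and it rarely removed the heterogeneity that triggered it. Under the assumed SDs the effect runs from negligible (normal data with modest SD ratios, or the largest group the most variable) to severe (lognormal data, 0.17 to 0.42). Repeat runs can move individual entries by about 0.02.

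The conclusion is confined to the hypothesis of equal arithmetic means in multi-group comparisons. It does not extend to positive markers with a common log-scale SD or, directly, to the multivariate selection of biomarkers. It is a worthwhile correction to supporting analyses, not a flaw in the study's core.

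**What to change.** Delete the Levene-then-log sentence. In its place:

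1. Use Welch ANOVA, with Games-Howell for pairwise comparisons, as the default for multi-group comparisons, without a variance pre-test.
2. List in advance the variables to be analysed on the log scale, limited to positive, skewed assay measures such as insulin, HOMA, triglycerides, cytokines and omics intensities, and report those results as geometric means or ratios. Leave SD scores and any other variable that can be zero or negative untransformed.

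Heteroscedasticity-consistent standard errors for the regression and ANCOVA models are optional.

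The cost is a change of wording and a slight loss of power when variances are in fact equal. No data collection or sample size changes.

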Because of the multifaceted nature of homeostasis, omics technologies, such as transcriptomics and metabolomics that broadly analyse functional genomic responses may be particularly valuable for the identification and characterization of biomarkers of PA on health. Peripheral blood cells (PBC) or the subpopulation of mononuclear cells within them (PBMC, including lymphocytes and monocytes) are an attractive source of biomarkers, particularly transcriptomic-based biomarkers because they can be easily obtained by minimally invasive techniques (12, 13). These cells travel through the blood, respond to external and internal factors, and their gene expression profile can partly reflect the expression profile of other tissues and be indicative of metabolic, physiological, and pathological states, as suggested by studies in animal models (14–17) and in humans (18–20). Moreover, PBMC were recently shown to be able to functionally reflect differences in fitness in adults (21). Hence, changes in gene expression in blood cells may inform on physiopathological states and may also have a predictive component (18, 22, 23). The use of PBC as a source of transcriptome markers concerning PA in children/adolescents is almost unexplored so far. In a recent study in children, we have described changes in PBC gene expression associated with low PA, which may be related to the cardiometabolic health effects of PA (24). The INTEGRActiv study will help to validate levels of our previously identified transcripts as indicators of low PA and to identify other potential biomarkers by using targeted and untargeted analyses. Functional links of the encoded transcripts/proteins with cardiovascular and endocrine markers may give information on the effects of PA on body health and will be further explored through literature and data mining/integration.

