##### Blood sample collection

2.3.2.4.

PBC will be obtained via antecubital fossa venipuncture in the early morning, under fasting conditions. Blood samples will be collected in PAX tubes, to allow optimal conservation and extraction of RNA from PBC for gene expression analyses, and in tubes containing or not anticoagulants (heparin) to obtain plasma and serum, respectively, for analyses of biochemical parameters, miRNA, cytokines, and metabolomics. Circulating biochemical parameters analyzed will include those classically related to metabolic syndrome; abnormal values will be defined from normative data (51).

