-Glucose, insulin, lipid profile (total, LDL, and HDL-cholesterol; triglycerides), uric acid and creatinine levels will be evaluated in plasma samples of all subjects of the core cohort using standard automated laboratory enzymatic methods. Insulin resistance will be assessed by the homeostatic model assessment (HOMA) index.-Plasma levels of circulating myokines and adipokines of special relevance, such as contraction-induced myokines, myokines involved in muscle-adipose tissue crosstalk, and main regulatory adipokines (Irisin, Interleukin-6 and 15, myostatin, FGF21, leptin, adiponectin, etc.) will be measured using commercial assay kits based on the Luminex® xMAP® technology, and ELISA kits in all subjects of the core cohort.-Whole-genome transcriptomic analysis of PBC samples will be performed by next-generation RNA Sequencing (RNA-Seq) in a representative subset of the core cohort (90 subjects). RT-qPCR analysis of the expression of the most remarkable genes (i.e., those most physiologically plausible and affected) identified in the unbiased transcriptomic study will be used to validate the results in all subjects of the core cohort.-Combined untargeted and targeted metabolomics and lipidomics analysis of plasma will be performed in all subjects of the core cohort by a LIMeX-4D workflow with 4 different liquid chromatography–mass spectrometry (LC-MS) based methods to annotate a wide range of complex lipids, polar metabolites, and exposome compounds (mainly food components and drugs) (65, 66). Promising biomarkers originating from untargeted metabolomics/lipidomics will be quantified using the reference standardization approach (67).-For circulating miRNA analysis, RNA will be extracted from plasma samples using the RNAeasy serum/plasma Kit (Qiagen). A miRNome analysis (around 2000 miRNAs) will be assessed in plasma samples of a representative subset of the core cohort (15 of each of the 6 groups), using miRNA sequencing. The most remarkable miRNAs identified (up to 20) will be analysed in the whole cohort by RT-qPCR.Candidate biomarkers emerging from phase 1 will be measured in plasma and PBC of the subjects in the educational intervention (phase 2) study, at the end of it, using ELISA, RT-qPCR, or biochemical assays, depending on the marker, as above described.

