#### Integrated analysis

2.6.1.

Data from the PA endpoints (PA, muscular fitness, and CRF describing variables) collected for each individual will be mapped in a principal component analysis plot. Hierarchical cluster analysis will be applied to the PCA scores in order to extract 3 clusters corresponding to low, medium, and high PA scores. The significant differences between the group of individuals will be challenged in a supervised partial-least square discriminant analysis (cross-validation ANOVA and permutation test). All the collected biological data, whether clinical or omics, will be examined in each of the 3 groups of individuals defined therefrom (low, medium, and high PA outcomes). Variables selection to fit the class assignment will be performed independently for each kind of variable with a sight of sparsity. PLS-discriminant analysis (orthogonalized or not), sparse-PLS, and machine-learning methods such as random forest will be applied and resilient variables, selected with all the methods, retained. Statistical models will be built on 4/5 of the population, and their performance assessed by predicting the 1/5 unknowns. This will be iterated 10 times. Complementary AUROC analyses will confirm biomarkers selection robustness. The most resilient variables (expected ∼20 variables from any origin) will be saved, and computed in a final PLS-discriminant analysis. From there, an equation calculated from the beta score of the PLS algorithm and the variable values will be established (using the NIPALS algorithm) to give each individual a score value (with 95% confidence intervals) that fits its PA class (e.g., low, medium, high). This equation will be challenged in the subgroup of the core cohort after the educational intervention. Also, the predictive robustness of the individual score value will be challenged to identified confounding factors (BMI, age, pubertal state, and gender, diet and lifestyle-related factors including sleep behaviour) in a logistic regression model.

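### Gene expression in mixed blood cells is compared between groups without leukocyte composition as covariate or sensitivity analysis, so pathway conclusions could be misattributed to gene regulation

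*Protocol article*

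**What the plan says.** Section 2.3.2.4 (Blood sample collection) fixes the specimen: "Blood samples will be collected in PAX tubes, to allow optimal conservation and extraction of RNA from PBC for gene expression analyses". It describes no cell separation. The Introduction shows that the specimen is understood to be a mixture, since it speaks of "Peripheral blood cells (PBC) or the subpopulation of mononuclear cells within them (PBMC, including lymphocytes and monocytes") as sources of markers, and it is the wider PBC population that is assayed.

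Section 2.5 plans RNA-Seq "in a representative subset of the core cohort (90 subjects"), then RT-qPCR of the most notable genes in the whole core cohort of 180. The blood measures listed there are plasma biochemistry, myokines and adipokines, metabolomics, lipidomics and miRNA. A blood count or leukocyte differential is not mentioned.

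Section 2.6 foresees contrasts by activity and body composition ("For multi-group comparisons depending on PA levels, body composition, or other health-related parameters available"). Differential expression is tested by t-tests "such as Student's or limma, ANOVA, and false discovery rate (FDR) correction", followed by enrichment and pathway analysis. ANCOVA with BMI, age and gender as example covariates is available where judged appropriate.

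Section 2.6.1 clusters the children to "extract 3 clusters corresponding to low, medium, and high PA scores" and selects variables against those classes. The resulting score "will be challenged to identified confounding factors (BMI, age, pubertal state, and gender, diet and lifestyle-related factors including sleep behaviour"). Section 2.1 gives a similar confounder list. Neither list includes cell composition. Later in 2.6.1 and in the Discussion, the biological variables are to be read as molecular regulation at pathway level and as mechanistic information on PA and health.

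**The concern.** A transcript level in mixed blood is a weighted average over cell types, with the cell shares as weights. It can differ between two groups because cells express the gene differently or because the shares differ. The planned tests cannot tell these apart.

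The later safeguards do not separate them either:

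- FDR control limits chance findings. A difference in bulk RNA caused by composition is real, so it is not a chance finding.
- RT-qPCR measures the same mixed RNA and would reproduce the difference.
- Cross-validation and agreement between selection methods favour stable signals, and genes of one lineage move together.

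What is at stake is interpretation. The Introduction expects of blood cells that "their gene expression profile can partly reflect the expression profile of other tissues and be indicative of metabolic, physiological, and pathological states". If part of the signal is cell mix, enrichment analysis may present immune pathways as the mechanism of PA. The score is also to be challenged after the 6-month intervention, when a change in cell mix unrelated to activity could move it.

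**Working it through.** The documents state no figure on this point, so there is none to reproduce. The check asks how often a gene with no change per cell would be declared different.

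**From the documents:** 90 sequenced children; three PA classes; nominal threshold 0.05.

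**Assumed (not in the documents):** equal classes, so 90/3 = 30 per class; neutrophil share f with mean 0.52 and SD 0.09; shift s between two classes of 0 to 0.08; expression in neutrophils k = 1, 4 or 10 times that in other cells; residual SD 0.25 on the log2 scale.

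**Model:** log2 expression = log2(f·k + 1 − f) + noise, with no PA effect inside any cell.

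**Hand calculation for s = 0.05:**

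- k = 4: difference = log2(0.57×4 + 0.43) − log2(0.52×4 + 0.48) = log2(2.71/2.56) = 0.082. Slope in f at 0.52 = 3/(2.56 × 0.693) = 1.69, so the SD due to share is 1.69 × 0.09 = 0.152. Total SD = √(0.152² + 0.25²) = 0.293. Standardised difference d = 0.082/0.293 = 0.28. A two-sample t-test at 30 v 30, two-sided 0.05, rejects in about 19%.
- k = 10: difference = log2(6.13/5.68) = 0.110. Slope = 9/(5.68 × 0.693) = 2.29, share SD 0.206, total SD 0.324, d = 0.34. Rejection about 25%.

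**Simulation of the same model** (20,000 replicates unadjusted; 3,000 with f as a covariate):

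| Shift in share | k | Unadjusted, P < 0.05 | Unadjusted, P < 0.001 | Adjusted for f, P < 0.05 |
|---|---|---|---|---|
| 0 | 4 / 10 | 4.9% / 4.8% | 0.1% / 0.1% | 5.2% / 5.6% |
| 0.02 | 4 / 10 | 6.9% / 8.6% | 0.2% / 0.3% | 5.1% / 4.3% |
| 0.05 | 4 / 10 | 19.6% / 26.0% | 1.3% / 2.3% | 5.2% / 5.0% |
| 0.08 | 4 / 10 | 40.0% / 54.7% | 5.1% / 10.3% | 4.9% / 5.1% |

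Genes expressed equally in all cells (k = 1) stay at about 5% throughout. The hand calculation and the simulation agree.

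**RT-qPCR step.** If all 180 children fall into three equal classes (180/3 = 60 each, assumed) and the residual SD is unchanged, the same d of 0.28 and 0.34 are declared different at P < 0.05 in about 33% and 46%. Measuring the same RNA in more children therefore raises the chance of confirming a composition effect.

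**The case against.** The strongest reply is that this is a condensed article. Covariates in a limma model are commonly left to a fuller document, the ANCOVA covariates are given only as examples, and deconvolution of RNA-Seq needs no design change. That stands to this extent: the article does not rule out the adjustment, and an unlisted blood count is one not mentioned, rather than one known not to be taken. It does not remove the point. The article names its confounders twice without composition and moves from bulk expression to mechanism.

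Partial controls exist: an early-morning fasting draw, exclusion of regular medication and reported pathologies, and possible adjustment for BMI, age and gender. They reduce the problem, but they do not measure cell shares. BMI adjustment also cannot help where the contrast is itself between BMI groups.

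A reader might infer that composition shifts will certainly be reported as PA-regulated genes. The documents do not support that. They give no leukocyte data by PA class, and with no shift the error rate is nominal.

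A reader might also take a larger figure. A lymphocyte difference of 3 to 5 points with SD 8 (both assumed) gives d = 3/8 = 0.375 to 5/8 = 0.625, and 30% to 66% at P < 0.05 with 30 v 30. That is a ceiling: it allows no other source of variation and uses an unadjusted threshold, although FDR is planned. At P < 0.001 the same differences give 3% to 16%.

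Finally, a transcript driven by composition can still predict PA class. That is right, and it confines the harm mainly to claims about regulation and pathways, and to reading changes in the score at 6 months.

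**Conclusion.** The point holds as a risk of misinterpretation. The article measures expression in a cell mixture, compares it between groups and draws pathway conclusions, and names no step that separates a change in cell mix from a change in expression per cell. FDR and RT-qPCR on the same RNA cannot do this.

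The size is unknown. Under the stated assumptions, a 5-point shift in neutrophil share gives about 20% to 26% per cell-type-specific gene at P < 0.05. It is near 5% with no shift and lower at stricter thresholds. The result depends on composition differing between the groups, on the gene being cell-type specific, on about 30 children per class (clusters need not be equal), and on the assumed SDs. No figure in the article is wrong, and the predictive use of the markers is not invalidated.

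**What to change.** In section 2.6, state that leukocyte fractions will be estimated for each sequenced sample by deconvolution of the planned RNA-Seq data. Repeat the limma and enrichment analyses with the fractions as covariates, and report adjusted beside unadjusted results. Where feasible, add a few lineage-marker genes to the RT-qPCR panel at baseline and at 6 months, so that the wider cohort and the follow-up score can be examined in the same way.

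Describe as PA-related gene regulation only the genes that persist after adjustment. Genes that do not persist may stay as predictive markers, labelled as possibly reflecting cell composition.

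The cost is analysis time, a few qPCR wells and some loss of precision from the added covariates; no extra visit or blood draw is needed. Composition may itself mediate an effect of PA, in which case adjustment removes part of a true effect. For that reason both analyses should be shown and the adjusted one should not replace the other.
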